### 2.7. Randomization

Randomization will be conducted using a random number table to assign patients to the two groups. Firstly, block size of 4 will be generated by a computer and 200 patients will be randomly assigned to the two groups in a ratio of 1:1 after acquiring their written informed consent to join a group, which ensures equal numbers of patients assigned to both groups at designated time intervals. Patients of the mild, moderate, and severe categories will be assigned equally to the two groups.

### 2.8. Blinding

In this trial, investigators who manage patients with acupuncture and moxibustion are unaware of the allocation of patients because they will be treated with other patients in the clinic. Investigators who assess these patients during the follow-up are also blinded. The statistician is also unaware of the allocation. But patients are aware of their allocation. To minimize the impact of patients’ awareness of their allocation, they will be managed at different time points so that they are unaware of the treatment options of the other group. For patients in the same group, they will be treated in the same room and no patients from the other group will be present.

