### 2.3. Interventions

In the conservative medical treatment group, α-blockers, 5α-reductase inhibitors, and phosphodiesterase type 5 inhibitors are prescribed by the investigators based on individual conditions. Acupuncture or moxibustion is not allowed in this group. Patients in this group will take conventional medicines. They will be explained how the medications work and their potential side effects.

In the combined therapy group, patients will receive simultaneous acupuncture and moxibustion. The moxa segment is burnt and attached to the acupuncture needle (see Fig. 2).

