**Figure 2. F2:**
[figure not shown]
Diagram of warming acupuncture and moxibustion.

Acupoints include: Zhongji (RN 3), Qihai (RN 6), Shenshu (BL 23, bilateral), Shuidao (ST 28, bilateral), Pangguangshu (BL 28, bilateral). Qihai is 1.5 *cun* inferior to the umbilicus along the anterior midline. The acupuncture needle is inserted into the body with the tip reaching a depth of 1 to 1.5 *cun*. One *cun* is defined as the width of the 1st interphalangeal joint of the patient. Zhongji is 4 *cun* inferior to the umbilicus along the anterior midline. The needle reaches a depth of 0.5 to 1*cun*. Shuidao is 3 *cun* inferior to the umbilicus and 2 *cun* lateral to the midline. The needle tip reaches 1 to 1.5 *cun*. Shenshu is 1.5 *cun* lateral to the spine of the 2nd lumbar vertebra on the back. The acupuncture needle tip reaches a depth of 1 *cun*. Pangguangshu is 1.5 *cun* lateral and inferior to the spine of the 2nd sacral vertebra on the back. The acupuncture needle tip reaches 1 *cun*. When patients have a feeling of “Teh Chi”, such as heaviness, numbness, and swelling, the needles will be kept in situ and burning moxa attached to the end of the needle. The moxa will be changed after burning out until 60 minutes are reached. These patients will be treated with the combined therapy once a week for 18 consecutive weeks. Patients in the combined therapy group will be managed by an experienced TCM doctor. Patients receiving this treatment will be managed in the same room. Communication between these patients will not impact their adherence.

Before the trial starts, patients will be briefed on our design and they have the choice to join either of the group, but which is better is not known before completing this trial. Therefore, they will be assigned to the two groups in a ratio of 1:1 after this briefing. Patients are encouraged to complete the trial with good adherence. As stated above, patients in the same group will be managed in the same room to minimize the impact of the selection of their therapies.

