### 2.4. Outcome measures

Primary and secondary outcomes will be evaluated by independent outcome assessors. They are well trained clinicians and familiar with these outcome measures and blinded to the randomization procedure. The primary outcome IPSS will be assessed using a questionnaire, secondary outcomes such as maximum flow rate (Qmax), post-voiding residual urine volume, and average flow rate (Qave), time to maximum flow, and voiding time will be measured through ultrasound examination at recruitment and 18 weeks after the trial starts. The evaluation results and time chart are as follows (Fig. 3).

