#### 2.4.1. Primary outcomes

The IPSS at 18 weeks after the start of the trial will be used to assess the severity of symptoms and treated as the primary outcome. The IPSS has 8 questions with each of the first 7 questions scored 0 to 5, resulting in a sum of 0 to 35. These questions are about urinary symptoms for patients to tick one out of six answers. These include: frequency, incomplete emptying, intermittency, weak stream, urgency, straining, and nocturia. A total score of <7 is ranked mild, 8 to 19 moderate, and 20 to 35 severe. The 8th question is about the quality of life perceived by the patients, which ranges from 0 to 6, corresponding to delightful to terrible quality of life.

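### The protocol calls the acupuncture therapists blinded, which the design does not allow, and the blinding that remains does not protect a primary IPSS ticked by patients who know their arm

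*Protocol article*

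**What the plan says.** Protocol article, section 2.8, makes four statements about blinding.

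- Therapists: "investigators who manage patients with acupuncture and moxibustion are unaware of the allocation of patients", and the reason given is "because they will be treated with other patients in the clinic".
- Follow-up assessors and the statistician are also said to be blinded.
- Patients are not: "But patients are aware of their allocation".
- To limit the effect of this, the arms are scheduled at different times, so that patients should not learn what the other group is offered. Within an arm, "they will be treated in the same room and no patients from the other group will be present".

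Section 2.3 says of the control arm: "Acupuncture or moxibustion is not allowed in this group". Of the other arm it says: "Patients in the combined therapy group will be managed by an experienced TCM doctor". It also says that patients are briefed on the design before they are assigned.

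Section 2.4 has independent assessors evaluate the primary and secondary outcomes and describes them as "blinded to the randomization procedure". Section 2.4.1 makes the 18-week IPSS the primary outcome and describes its questions as being "for patients to tick one out of six answers".

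The limitations in section 3 cover the single centre, the sample size and carry-over of earlier medicines. They do not mention blinding.

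**The concern.** Two things look wrong. First, the protocol claims a blinding property for the therapists that the design cannot have, because the treatment itself shows the arm. Second, the blinding that is feasible, of assessors and statistician, acts after the point at which bias could enter the primary outcome. The patient supplies the IPSS answers and knows which treatment he received.

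At stake is what an IPSS difference can be said to show. One arm receives a new treatment in weekly 60-minute sessions for 18 weeks. The other takes medicines from conventional classes, after an entry criterion of at least 3 months on western medicines. Any difference in expectation or attention between the arms enters the IPSS comparison directly and cannot be separated from a treatment effect. A reader of section 2.8 who takes the stated blinding at face value would credit the primary result with more protection than it has.

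**Working it through.** **1. Therapist blinding: the passages side by side.**

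- Section 2.3: controls may not receive acupuncture or moxibustion.
- Section 2.3: the combined-therapy group is managed by a TCM doctor, who inserts the needles and attaches the burning moxa.
- It follows that a trial patient who is being needled is in the combined-therapy arm.
- The reason in section 2.8 is that trial patients are treated among other clinic patients. If those are non-trial patients, the therapist may not know who is in the trial. Once a patient is known to be a participant, his arm is known too. The reason can hide trial membership but not allocation.

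**2. Source of the primary outcome.**

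- Section 2.4.1: the patient ticks the IPSS answers.
- Section 2.8: the patient knows his allocation.
- It follows that a shift in reporting is already in the score when an assessor receives it or the statistician analyses it. Blinding either of them does not remove it.

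**3. The mitigation.** Section 2.8 relies on patients not knowing what the other group is offered. Section 2.3 has them briefed on the design beforehand. Both cannot hold, and separate rooms and times do not undo the briefing.

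**4. The plan's own figure, used as input below.** Section 2.6 gives 80 evaluable patients per group for 80% versus 60%, alpha 0.05 and power 0.80. With unpooled variance:

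n = (1.960 + 0.842)² × (0.8×0.2 + 0.6×0.4) / 0.20² = 7.85 × 0.40 / 0.04 = 78.5, so 79 per group.

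The pooled-variance form gives 82. The stated 80 lies between the two, and 80 / (1 − 0.20) = 100 per group. The blinding point does not depend on this calculation; it only supplies n = 80.

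**5. Illustration of scale (bias assumed, not from the documents).** Take no true effect, 80 per arm, a two-sided 0.05 test and the normal approximation, with b the between-arm reporting shift in SD units.

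SE = √(2/80) = 0.158 SD

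P(reject) = 1 − Φ(1.960 − b/SE) + Φ(−1.960 − b/SE)

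| Assumed shift b (SD) | b/SE | P(reject) |
|---|---|---|
| 0 | 0 | 0.050 |
| 0.1 | 0.632 | 0.097 |
| 0.2 | 1.265 | 0.244 |
| 0.3 | 1.897 | 0.475 |

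With all 100 per arm evaluable, shifts of 0.1, 0.2 and 0.3 SD give 0.109, 0.293 and 0.564. A larger sample makes a false-positive result from a fixed bias more likely.

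**The case against.** The strongest reply is that the protocol is open about the patients: it says they are unblinded and lists measures to limit the effect. An open design may be unavoidable with needles and burning moxa. Blinding of assessors and statistician is good practice and may well protect the flow and residual-urine measurements. All of that stands. The fault lies in the therapist claim, the mitigation claim and the missing caveat on IPSS, not in the choice of an open design.

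A reader might also infer several stronger points that the documents do not support.

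- *Section 2.8 contradicts itself about who is in the room.* The other clinic patients can be non-trial patients, who may be present while control-arm patients are absent. There is no strict contradiction.
- *The assessors are unblinded too.* Nothing shows that the independent assessors see the treatment or learn the arm. Section 2.4 names only the randomization procedure, but in section 2.8 the sentence on assessors directly follows one about allocation and reads naturally as blinding to allocation. The wording in section 2.4 is loose and should be aligned.
- *Controls have no contact with staff.* The combined arm's sessions add up to 18 × 60 minutes = 18 hours. The article gives no control visit schedule, but it describes prescribing and explanation by investigators. Zero contact is not established.
- *The false-positive rates estimate this trial's error.* They do not. Both the size of the shift and its direction are assumptions.
- *Qmax must be ranked first, with a baseline-adjusted model.* That would be a preference. Section 2.9 plans a t test and a GLMM, and ranking of supportive outcomes may sit in an analysis plan that is not shown.

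**Conclusion.** The point holds as wrong as written. The statement that therapists are unaware of allocation is incompatible with section 2.3. The statement that patients do not know the other group's options conflicts with the briefing in the same section. The primary IPSS is an unblinded patient report, and the remaining blinding does not protect it. These conclusions rest on the text alone.

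The size of the effect on the result is unknown. The illustration (about 10%, 24% and 47% false positives at assumed shifts of 0.1, 0.2 and 0.3 SD, against a nominal 5%) assumes no true effect, 80 evaluable per arm and a normal approximation. It shows only that a modest reporting shift would matter at this sample size.

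The conclusion does not extend to the instrument-measured secondary outcomes, for which blinding of assessors to allocation remains useful.

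**What to change.** 1. In section 2.8, delete the claim that therapists are unaware of allocation and the claim that patients are unaware of the other group's options.
2. State that patients and therapists are unblinded, and that outcome assessors and the statistician are blinded to allocation. Change section 2.4 to say the same of the assessors.
3. Label IPSS an unblinded patient-reported outcome in section 2.8, and add this to the limitations in section 3.
4. State in advance that an IPSS difference will be interpreted as including possible expectation and attention effects. Say that it will be read beside the instrument-measured outcomes already planned (Qmax, Qave, residual urine), taken by assessors blinded to allocation.

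These are changes of wording and interpretation. They need no new measurements, patients or analyses. The downside is a more modest claim from a positive IPSS result.

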### 2.9. Statistical method

Results collected will be initially validated by two investigators before statistical analyses. Data analysis will be conducted using IBM SPSS (version 20.0) for Windows (SPSS Inc., Chicago, IL) by a statistician who is blinded to patients’ information. Continuous variables will be presented as mean ± SD or median with an interquartile range (IQR). Information of patients at enrollment will be compared using the Mann-Whitney *U* test or using the *t* test for continuous variables, and the Fisher’s exact test or χ^2^ for categorical variables. Two-side Student’s *t* test will be used to compare continuous variables like IPSS, maximum flow rate, voiding time, average flow rate, post-voiding residue urine volume, and time to maximum flow 18 weeks after treatment. Longitudinal analysis of IPSS, Qmax, voiding time, post-voiding residual urine, Qave, and time to maximum flow were done with a GLMM approach, accommodating data with nonequidistant repeated measures of time and missing values. *P* < .05 (two-sided) is considered statistically significant.

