## 2. Study design and Methods

### 2.1. Design and setting

This RCT is a single-center, investigator-initiated study, aiming to examine the efficacy of combined therapy of acupuncture and moxibustion in treating BPH. This efficacy will be compared with that of conservative western medical treatments alone. A calculated number of 200 BPH patients will be enrolled from the Urology and the Traditional Chinese Medicine clinics of Shanghai Fourth People’s hospital. BPH patients will be randomly assigned to these two groups using a random number table in a ratio of 1:1. A block size of 4 will be generated using a computer, which ensures equal numbers of patients assigned to both groups at designated time intervals. Randomization will be stratified based on the severity of symptoms, where a total score of the baseline International Prostate Symptom Score (IPSS) <7 is considered mild, 8 to 19 moderate, and 20 to 35 severe. Written informed consent to participate in this study will be obtained from all patients. The process is shown in Figure 1.

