#### 2.4.2. Secondary outcomes

The volume of residue urine in the bladder will be measured through the ultrasound examination before and after treatment and this difference will be compared between groups.

The peak and the average urine flow rates will be calculated using the Qmax and the Qave collected from the urodynamic examination.

Voiding time, time to completely empty the bladder, and the time to maximum flow will be measured during the urodynamic examination.

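### The primary week-18 IPSS comparison is an unadjusted t test although randomisation is stratified on baseline IPSS severity, and the plan does not say whether the t test or the GLMM decides the trial

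*Protocol article*

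**What the plan says.** All references are to the protocol article.

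- **Primary outcome (2.4.1):** IPSS at week 18 is the primary endpoint; up to its last word the sentence reads "The IPSS at 18 weeks after the start of the trial will be used to assess the severity of symptoms and treated as the primary".
- **Randomisation (2.1):** "Randomization will be stratified based on the severity of symptoms", defined by baseline IPSS total. Allocation is 1:1 in blocks of 4 (2.1 and 2.7).
- **Main comparison (2.9):** a two-sided Student's t: "test will be used to compare continuous variables like IPSS". The same sentence covers the flow, timing and residual-volume measures, all 18 weeks after treatment. No covariate or stratum is mentioned.
- **Second analysis (2.9):** longitudinal analyses of IPSS and the same secondary outcomes "were done with a GLMM approach, accommodating data with nonequidistant repeated measures of time and missing values". No contrast or covariates are given, and the two analyses are not ranked. One two-sided 5% rule closes the section.
- **Residual urine (2.4.2):** measured "before and after treatment and this difference will be compared between groups". Section 2.9 instead lists it among the variables compared at 18 weeks.
- **Sample size (2.6):** 80 per group from success rates of 80% and 60%, raised to 100 per group for dropout.

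**The concern.** Baseline IPSS is needed for eligibility (a score above 8, section 2.2.2) and for stratification, so it is on file for every randomised patient. Symptom scores taken 18 weeks apart in the same men are normally correlated, so baseline explains part of the outcome variance. A Student's t test cannot use that information.

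There is also a mismatch between design and analysis. Stratified blocks remove most chance imbalance in severity, so the difference in means varies less from trial to trial than under simple randomisation. The t test's standard error still counts the between-stratum variation. It is therefore too large, the interval too wide and the test's true size below 5%.

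Separately, with two unranked analyses of the primary outcome, the plan does not fix which estimate is the trial's result. Section 3 itself calls the sample relatively small and expects that a benefit may be missed, so wasted precision matters here.

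**Working it through.** **1. The plan's own figure.** With 80% v 60%, two-sided alpha 0.05 and power 0.80:
- unpooled: n = (1.960 + 0.842)² × (0.8×0.2 + 0.6×0.4) / 0.20² = 78.5, so 79 per group; the pooled formula gives 82;
- power at 80 per group is 79.4%;
- 80 / (1 − 0.20) = 100.

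The figures reproduce, but they power a binary rate. The plan states no IPSS difference or SD, so an illustrative effect is needed. With 80 completers per arm, a t test has 80% power at √(2/80) × (1.960 + 0.842) = 0.443 SD (normal approximation), or 0.446 SD using the t distribution. I use 0.446.

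**2. Assumptions not in the documents.**
- The correlation r between baseline and week-18 IPSS: 0.3, 0.5 or 0.7.
- Normally distributed baseline, with the moderate/severe cut 0.25 SD above the mean. The entry criterion leaves only these two strata populated.
- 200 randomised in stratified blocks of 4, with 20% lost at random (160 completers). The 20% is one of two dropout figures in 2.6; the other is 25%.

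**3. How far the t test's standard error is too large.** The share of baseline variance explained by the two strata is φ(0.25)² / [Φ(0.25)(1 − Φ(0.25))] = 0.3867² / (0.5987 × 0.4013) = 0.622. Random loss of 20% undoes one fifth of the balancing, leaving 0.8 × 0.622 = 0.498. The ratio of reported to true standard error is then 1/√(1 − 0.498 r²):
- r = 0.3: 1/√0.955 = 1.023
- r = 0.5: 1/√0.876 = 1.069
- r = 0.7: 1/√0.756 = 1.150

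True size is 2[1 − Φ(1.960 × ratio)] = 4.5%, 3.6% and 2.4%. Simulation under the same loss gives 4.6%, 3.5% and 2.4%.

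**4. Power at 0.446 SD.** The nominal standard error is √(2/80) = 0.158 SD, so effect/SE = 2.82.
- t test: Φ[(2.82 − 1.96) × ratio] = 81%, 82% and 84%.
- Adjusted: Φ[2.82/√(1 − r²) − 1.96] = 84%, 90% and 98%.

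The approximation ignores small-sample terms. Simulation gives slightly lower values:

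| Assumed r | t test SE too large by | t test true type I error | Power, t test | Power, adjusted |
|---|---|---|---|---|
| 0.3 | 2% | 4.6% | 80% | 83% |
| 0.5 | 7% | 3.5% | 82% | 90% |
| 0.7 | 15% | 2.4% | 84% | 97% |

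**5. Width of the interval.** Relative to the adjusted interval, the unadjusted one is wider by 1/√(1 − r²) − 1 = 4.8%, 15.5% and 40.0%.

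**6. Two analyses.** One possible form of the GLMM, a group-by-time contrast on two assessments, amounts to comparing change scores. Simulated with 160 patients and no loss, at r = 0.3, 0.5 and 0.7:
- power of t test v change contrast: 80% v 67%, 81% v 81%, 85% v 96%;
- type I error if success is claimed when either is significant: 5.3%, 5.0% and 5.4%, against 4.0%, 3.2% and 2.0% for the t test alone.

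The two analyses can disagree, and which is stronger depends on an unknown correlation. The combined error rate nevertheless stays close to 5%.

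**The case against.** **It is only an efficiency matter.** This stands. The t test is unbiased under randomisation and its size error is conservative. A reader might infer that the analysis is invalid or raises false positives; the plan does not support that.

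**The gain rests on an unstated correlation.** This also stands. Restricting entry to IPSS above 8 narrows the baseline range and may lower the correlation. At 0.3 the gain is about 3 points of power. Setting adjusted power against a flat 80% would also overstate the gain, because stratification already lifts the t test to about 84% at r = 0.7.

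**The t test can be read as primary.** It is the analysis tied to 18 weeks, as is the primary outcome, while the GLMM is called longitudinal. That is a fair reading, but the text does not say it. A reader might infer serious type I error inflation from choosing between the two. In the one form tried the rate was only 5.0% to 5.4%; other forms could differ.

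**The GLMM may use baseline and incomplete patients.** Section 2.9 describes it as "accommodating data with nonequidistant repeated measures of time and missing values". So one cannot say that missing data are ignored throughout, or that baseline is unused in every analysis. The criticism is confined to the t test and the missing ranking.

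**The visit schedule.** Section 2.4 gives assessments "at recruitment and 18 weeks after the trial starts", and a reader might infer that the GLMM's repeated, unequally spaced measures contradict this. That does not hold: the section refers to a time chart (Figure 3) that is not shown and may contain further IPSS visits, and the quoted timing may belong only to the secondary measures.

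**Residual urine may be condensed wording.** Possibly, and it is one secondary outcome. It is worth reconciling but does not carry the point.

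**Conclusion.** The point holds as one of efficiency and of an unfixed primary result. It rests on what section 2.9 states: a named test that cannot carry baseline or strata, and a second model on the same outcome with no order of precedence.

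The loss is small at a correlation of 0.3 and substantial at 0.7, where about 13 points of power (97% − 84%) are given up. These sizes depend on the assumed correlation, the assumed share of severe patients, random loss of 20% and an effect of 0.446 SD that the plan does not state. The direction does not depend on the exact values, provided that baseline and week-18 IPSS are correlated. The change should be made, but the plan is not invalid without it.

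**What to change.** In section 2.9:

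1. Name one primary analysis: ANCOVA of week-18 IPSS on treatment, continuous baseline IPSS and severity stratum. One mixed model with a fixed week-18 treatment contrast and the same adjustment would also serve. The two are similar but not identical, so choose one.
2. Report the adjusted mean difference with its 95% confidence interval as the trial's result.
3. Label the unadjusted t test and any other model as supportive.
4. Use the same form for each secondary outcome, adjusting for that outcome's own baseline. With baseline in the model, the treatment estimate is the same whether the response is the final value or the change, so sections 2.4.2 and 2.9 then agree on residual urine.

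The cost is a few sentences. The necessary IPSS data are already collected, and SPSS fits these models. The one added obligation is to state how missing week-18 scores enter the chosen model.

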#### 2.2.2. Inclusion criteria

Patients will be enrolled upon meeting the following criteria:

Males of 45 years or older.BPH diagnosed upon digital rectal examination.The measured volume of the prostate ≥30 mL.The maximum urinary flow rate <15 mL/second.BPH patients are willing to participate in this study.Continuous intake of western medicines for 3 months or more.Moderate to severe BPH (IPSS score >8).

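### The only test tied to week-18 IPSS is an unadjusted t test that ignores baseline IPSS, the stratification factor; it is valid but conservative, and its rank against the planned GLMM is unstated

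*Protocol article*

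**What the plan says.** - **Endpoint (2.4.1).** "The IPSS at 18 weeks after the start of the trial will be used to assess the severity of symptoms", and this is named as the primary outcome.
- **Week-18 comparison (2.9).** A two-sided Student's t "test will be used to compare continuous variables like IPSS, maximum flow rate, voiding time" and the remaining flow and residual-urine measures, 18 weeks after treatment. The sentence has no baseline or stratum term.
- **Second analysis (2.9, next sentence).** "Longitudinal analysis of IPSS, Qmax, voiding time, post-voiding residual urine, Qave, and time to maximum flow were done with a GLMM approach". The text adds that this handles unequally spaced visits and missing values. It does not list covariates, call the GLMM primary, or rank it against the t test.
- **Baseline data.** Outcomes are measured "at recruitment and 18 weeks after the trial starts" (2.4). Entry requires "Moderate to severe BPH (IPSS score >8" (2.2.2), so baseline IPSS is known for every patient.
- **Allocation.** "Randomization will be stratified based on the severity of symptoms" (2.1), defined by baseline IPSS category, and a "block size of 4 will be generated by a computer" (2.7). The listed categories include mild, but the entry rule leaves only moderate and severe.
- **Residual urine (2.4.2).** The before-to-after difference is to be compared between groups, whereas 2.9 lists the week-18 volume under the t test.

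**The concern.** The design balances the arms on baseline IPSS, and the one test attached to the primary time point then discards it. This has two consequences.

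1. Stratification removes some between-arm variation, but the two-sample t test still counts that variation in its standard error. Its p value is therefore too large on average, and its interval too wide for what the design delivers.
2. The remaining prognostic information in the continuous baseline score goes unused.

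Both matter here because the Discussion (section 3) itself calls the sample fairly small and worries about missing a real effect. The objective in 1.2 is also framed as being as effective as western medicine. An unnecessarily wide interval makes a non-significant result more likely, and such a result could be misread as support for that objective.

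**Working it through.** **1. The plan's own figure.** Section 2.6 gives 80 per group for 80% v 60%, two-sided α 0.05, power 0.80.

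- Pooled variance: n = [1.960·√(2·0.7·0.3) + 0.842·√(0.8·0.2 + 0.6·0.4)]² / 0.2² = 82 after rounding up.
- Unpooled variance: (1.960 + 0.842)²·0.40 / 0.04 = 79 after rounding up.
- Dropout: 80 / (1 − 0.20) = 100.

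The stated 80 and 100 reproduce to within 2 patients. They rest on response proportions, so they say nothing about the power of the IPSS t test.

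**2. Assumptions.** The documents give no IPSS standard deviation, no target difference and no correlation r between baseline and week 18. I take r = 0.3, 0.5 and 0.7. For power I use a reference effect that gives the unadjusted test 80% power at 80 per group: d = (1.960 + 0.842)·√(2/80) = 0.443 SD by the normal approximation, 0.446 SD by the noncentral t.

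**3. Precision with adjustment for baseline.** The variance is multiplied by 1 − r², the interval width by √(1 − r²), and the number needed for the same power is 80(1 − r²) per group. Power is evaluated at d/√(1 − r²).

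| r | 1 − r² | Interval width | Per group for same power | Power at 80 per group |
|---|---|---|---|---|
| 0.3 | 0.91 | ×0.95 (5% narrower) | 73 | 84% |
| 0.5 | 0.75 | ×0.87 (13% narrower) | 60 | 90% |
| 0.7 | 0.51 | ×0.71 (29% narrower) | 41 | 97.5% |

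**4. Calibration of the t test under this design.** The simulations used baseline IPSS limited to 9–35, strata 9–19 and 20–35, and permuted blocks of 4. One version randomised 200 with 20% random loss. The other used 160 completers with no loss after randomisation.

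| r | Type I error, 20% loss | Type I error, no loss | Reported SE / true SE, no loss |
|---|---|---|---|
| 0.3 | about 4.7% | 4.1% | 1.03 |
| 0.5 | about 3.7% | 3.1% | 1.10 |
| 0.7 | about 2.2% | 1.8% | 1.21 |

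The last two columns agree with each other. A standard error 1.10 times too large moves the effective critical value to 1.960·1.10 = 2.156, whose two-sided tail is 3.1%. At 1.21 it is 2.37, or 1.8%. Random loss loosens the balance within strata, which is why the error is nearer to 5% with dropout.

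Over other assumed baseline distributions with 20% loss, the type I error ran over 4.4–4.8%, 3.6–3.9% and 2.2–3.0%. The direction never changed. The model with treatment, stratum and baseline stayed at about 5% throughout (4.7–5.3%).

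**5. Simulated power at the reference effect.** The t test gave about 80%, 82% and 83% (up to 86% in one run at r = 0.7). The adjusted model gave about 83%, 90% and 97%.

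**The case against.** **The GLMM may already use baseline.** It is planned for IPSS, and recruitment is one of the measurement times, so depending on its specification it could recover much of the lost information. Covariates are commonly left to an analysis plan, which is not shown here. This stands in part. It rules out saying that the plan makes no use of baseline IPSS. It does not settle which analysis decides, because 2.9 states both for the same outcome and ranks neither. That the t test is primary is itself an inference from its match to the week-18 endpoint.

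**The t test is valid.** This stands. A reader might infer that the primary p value is invalid or the estimate biased. Neither follows. The test is unbiased over repeated randomisations and its error rate stays below 5%. Chance imbalance within strata adds noise, not bias, and stratification already limits it.

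**The correlation is unknown and may be low.** This stands. At r = 0.3 the miscalibration and the power gain (about 3 points) are small, and the IPSS entry rule narrows the baseline range, which tends to lower r. The striking figures need r near 0.7.

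**The power reference is borrowed.** This stands. The trial was sized on proportions. A reader might infer that it is underpowered for IPSS, but the documents cannot show that. The figures illustrate relative efficiency only.

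**The secondary outcomes differ.** This stands. A reader might extend the same loss to all of them. They are not the stratification factor, so the calibration argument reaches them only as far as they correlate with baseline IPSS. The gain from adjustment depends on each outcome's own unknown correlation. For residual urine, 2.4.2 already describes a before-to-after comparison.

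**Conclusion.** The point holds as one of efficiency and specification; it does not threaten validity. The only test linked to week-18 IPSS leaves out a variable that the design collects in everyone and stratifies on, and the plan does not say how that test ranks against the GLMM. On the assumed r of 0.3, 0.5 and 0.7, the t test runs at about 4.7%, 3.7% and 2.2% instead of 5%, and its interval could be about 5%, 13% and 29% narrower. For illustration, at 0.446 SD, adjustment raises power from about 80–83% to 83%, 90% and 97%. These sizes rest on the assumed correlation, an assumed baseline distribution and random dropout. The direction does not depend on which of the tried values is used, provided baseline IPSS predicts week-18 IPSS at all. The change should be made, because it costs almost nothing even if r is low.

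**What to change.** In 2.9, name one primary analysis: a linear model of week-18 IPSS on treatment, continuous baseline IPSS and the randomisation stratum (in effect moderate v severe). Report the adjusted mean difference with its 95% CI. State that the t test and the GLMM are supportive, and give the GLMM's covariates there or in the analysis plan.

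Use the same form for each secondary outcome with its own baseline value. For residual urine, reconcile the before-to-after difference in 2.4.2 with the week-18 value in 2.9; a model with baseline as covariate would serve both.

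The cost is wording in 2.9 and in the analysis plan, settled before the data are unblinded. It needs no extra patients, visits or measurements, and the named software fits the model.
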